## Abstract

**Background:**

Despite the health benefits of regular physical activity, most children are insufficiently active. Schools are ideally placed to promote physical activity; however, many do not provide children with sufficient in-school activity or ensure they have the skills and motivation to be active beyond the school setting. The aim of this project is to modify, scale up and evaluate the effectiveness of an intervention previously shown to be efficacious in improving children’s physical activity, fundamental movement skills and cardiorespiratory fitness. The ‘Internet-based Professional Learning to help teachers support Activity in Youth’ (*iPLAY*) study will focus largely on online delivery to enhance translational capacity.

**Methods/Design:**

The intervention will be implemented at school and teacher levels, and will include six components: (i) quality physical education and school sport, (ii) classroom movement breaks, (iii) physically active homework, (iv) active playgrounds, (v) community physical activity links and (vi) parent/caregiver engagement. Experienced physical education teachers will deliver professional learning workshops and follow-up, individualized mentoring to primary teachers (i.e., Kindergarten – Year 6). These activities will be supported by online learning and resources. Teachers will then deliver the *iPLAY* intervention components in their schools. We will evaluate *iPLAY* in two complementary studies in primary schools across New South Wales (NSW), Australia. A cluster randomized controlled trial (RCT), involving a representative sample of 20 schools within NSW (1:1 allocation at the school level to intervention and attention control conditions), will assess effectiveness and cost-effectiveness at 12 and 24 months. Students’ cardiorespiratory fitness will be the primary outcome in this trial. Key secondary outcomes will include students’ moderate-to-vigorous physical activity (via accelerometers), fundamental movement skill proficiency, enjoyment of physical education and sport, cognitive control, performance on standardized tests of numeracy and literacy, and cost-effectiveness. A scale-up implementation study guided by the RE-AIM framework will evaluate the reach, effectiveness, adoption, implementation, and maintenance of the intervention when delivered in 160 primary schools in urban and regional areas of NSW.

**Discussion:**

This project will provide the evidence and a framework for government to guide physical activity promotion throughout NSW primary schools and a potential model for adoption in other states and countries.

**Trial registration:**

Australia and New Zealand Clinical Trials Registry (ACTRN12616000731493). Date of registration: June 3, 2016.

## Background

Physical inactivity is a global pandemic, with “far-reaching health, economic, environmental and social consequences” [1]. Among children, the health benefits of physical activity are extensive and include improved physical fitness and bone health as well as reduced risk of obesity and cardiometabolic precursors of diseases such as type II diabetes [2, 3]. Physical activity may also improve psychological well-being and prevent mental health disorders such as depression and anxiety [3–5]. Recent evidence also indicates that, compared with their less active peers, physically active children can exert better cognitive control [6], are more engaged with school [7], and perform better on standardized tests of academic achievement [8].

The International Society for Physical Activity and Health [9] considers schools to be among the seven “best investments” for evidence-based physical activity promotion. Unfortunately, many schools are failing to provide children with sufficient opportunities to be active at school and do not equip them with the necessary skills and motivation to be active beyond the school setting [10, 11]. In systematic reviews, multi-component, flexible models were deemed more effective than single component models [12, 13]. Similarly, the US Centers for Disease Control and Prevention recommend schools deliver comprehensive school physical activity programs [14] that involve coordination across five components: (i) quality physical education (PE), (ii) activity during the school day, (iii) activity before and after school, (iv) staff involvement and (v) family and community involvement.

Despite convincing evidence of their effectiveness, few studies have implemented and evaluated comprehensive school physical activity programs. [15] Instead, most interventions have focused on one component of the school day (e.g., PE or recess/lunch breaks) [16, 17] and have neglected to address the multiple opportunities for physical activity promotion that exist within and beyond the school setting [18]. Among interventions that embraced a multi-component approach, few objectively measured effects on children’s physical activity (e.g., via accelerometers) [19].

The *SCORES* intervention was a comprehensive, multi-component physical activity and fundamental movement skills program for primary schools [20–22]. A socio-ecological model [23] provided the framework for the 12-month intervention, which consisted of components designed to engage teachers, students, parents and community sport organizations. Implementation strategies included: (i) professional learning and mentoring for teachers, (ii) feedback for teachers based on the quality of their PE and school sport, (iii) lesson resources for teachers, (iv) physical activity equipment, (v) school physical activity policy review and recommendations, (vi) training student leaders, (vii) parent engagement via newsletters, homework and information sessions, and (viii) engagement with local community sport. Our efficacy study [21] showed significant intervention effects at 12 months for cardiorespiratory fitness (5.4 laps; 95 % CI, 2.3 to 8.6), daily moderate-to-vigorous physical activity (12.7 mins/day; 5.0 to 20.5), and overall movement skill competency (4.9 units; -0.04 to 9.8). In addition, *SCORES* was delivered with a high degree of fidelity and teachers and students reported high satisfaction with the program.

There is a considerable gap between successful interventions like *SCORES*, and widespread dissemination in real world contexts [24, 25]. This is crucial, as to improve health of populations, interventions that have been effective in research settings must be delivered more broadly [26] and with less lag time between evidence generation and implementation. Indeed, there has been a proliferation of school-based physical activity intervention efficacy trials in recent years [18], yet these studies have made little impact on policy and practice [27].

In our project we will scale up and evaluate the effectiveness of a modified version of the *SCORES* intervention. The modified intervention centres around online delivery of professional learning to teachers. This customized, web-based delivery system was initially developed for a school-based physical activity intervention also led by our research team [28]. Teachers will deliver the intervention to students and parents and engage with community sport and recreation organizations. The modified intervention will be known as *iPLAY* (*I*nternet-based *P*rofessional *L*earning to help teachers to support *A*ctivity in *Y*outh) and will be among the first comprehensive school-based physical activity interventions with a large proportion of the program delivered online. A web-based delivery system is attractive as it may support scaling up and sustainability, and recent evidence indicates that online professional learning for teachers can be as effective as face-to-face training [29].

### Aims and hypotheses

We will conduct two complementary studies involving primary schools across New South Wales (NSW), Australia. In the first study, we will conduct a cluster randomized controlled trial (RCT) with a sample of 20 schools. The aim of this trial will be to evaluate the effectiveness and cost-effectiveness of *iPLAY* at 12 and 24 months, with cardiorespiratory fitness as the primary outcome. Key secondary outcomes will include objectively-measured moderate-to-vigorous physical activity, fundamental movement skills, cognitive control and student performance on standardized tests of numeracy and literacy. We hypothesize that:compared with the control condition, the *iPLAY* intervention will produce positive effects on children’s outcomes in the short-term (post-intervention, 12 months after baseline, primary endpoint for the trial),these benefits will be maintained 12 months after the end of the intervention (24 months after baseline), andthe intervention will represent value-for-money.

The aim of the second study will be to evaluate the intervention’s wide-scale implementation (scale up). To achieve this goal we will adopt the RE-AIM framework and assess Reach, Effectiveness, Adoption, Implementation, and Maintenance of *iPLAY* in 160 NSW primary schools (i.e., Kindergarten – Year 6).

## Methods

### Design

We will concurrently conduct two complementary evaluations (see Fig. 1):A cluster RCT involving 20 schools (1:1 allocation to intervention and attention control conditions) to evaluate the *E*ffectiveness and incremental cost-effectiveness of the *iPLAY* intervention, with cardiorespiratory fitness as the primary outcome.A scale-up implementation study will examine *iPLAY*’s *R*each, *A*doption, *I*mplementation and *M*aintenance with a reduced examination of *E*ffectiveness and cost-effectiveness. These aspects will be measured in 160 schools.

**Fig. 1 Fig1:**
[figure not shown]
Modified CONSORT Flow Diagram

All teachers in each school selected for the cluster RCT and scale-up implementation study will be invited to complete the *iPLAY* intervention (or attention control intervention for 10 schools in the cluster RCT). However, only the student cohorts in Years 3 and 4 at baseline will complete outcome assessments (i.e., students in Years 3 and 4 at baseline, students in Years 4 and 5 at post-intervention [12 months], students in Years 5 and 6 at maintenance [24 months]). These students will be available for assessment at all time-points (c.f. most Year 5 and 6 students will leave the school by 24 months), and will have the cognitive ability to complete the questionnaires (c.f., Years 1 and 2). In addition, these years represent the ideal period to develop fundamental movement skill competency [30], which may help prevent the decline in physical activity typically observed during the transition from childhood to adolescence [31].

### Recruitment, selection and randomization for both investigations

All government-funded NSW primary schools (*N* = 1,600) [32] will be invited to participate in the project. All schools will be eligible to participate in the scale-up implementation study, but those designated as ‘Schools for Specific Purposes’ (i.e., for students who require intensive levels of support) will not be eligible for the cluster RCT. Schools that participated in the original *SCORES* efficacy study [21] will be eligible for the scale-up implementation study, but will be excluded from the cluster RCT.

Schools will be recruited via presentations at conferences and meetings (e.g., regional meetings of the NSW Primary Principals Association) and advertisements sent by the NSW Department of Education and the Australian Council for Health, Physical Education and Recreation. We will also advertise via the NSW Department of Education Twitter feeds and Facebook pages. We aim to recruit a total of 180 schools (>10 % of the total number of NSW government-funded primary schools). From the schools that express interest prior to May 2016, we will use a computer-generated algorithm to randomly select 90 to form Cohort 1. Recruitment will continue through to March 2017 at which point we will randomly select 90 schools to form Cohort 2.

From within each cohort, we will select 10 schools to participate in the cluster RCT; the other 80 schools will participate in the scale-up implementation study. Selecting schools for the cluster RCT will involve a four-step approach. The aims of this process are to ensure that schools in the cluster RCT are: (i) broadly representative of schools in NSW and (ii) assigned to trial arms such that most school-level covariates (e.g., socioeconomic status [SES], geographic location) are balanced, thereby increasing the likelihood that children in the two conditions are similar on the outcome variables at baseline. The four steps are:*Stratification:* All schools that express interest in the study and are among the 90 selected to participate in each cohort will be stratified according to SES and geographic location. Given the number of schools is small, the stratification process will require relatively coarse groupings. The Index of Community Socio-educational Advantage (ICSEA) will serve as the SES variable. This index includes information regarding parental SES and Indigenous representation [33]. The index has a median of 1000 and ranges Australia-wide from 300 to 1300 indicating heavy negative skew [33]. NSW has a similar distribution ranging from 582 to 1202 with a median of 1003. We will split the sample into a higher SES stratum (ICSEA < =1003) and a lower SES stratum >1003. These strata will be further split by geographic distribution using the Australian Bureau of Statistics remoteness index by postcode. The index has 12 categories but this will be reduced to two: urban (less remote) and provincial (more remote). This process will produce four strata: (i) urban-higher SES, (ii) urban-lower SES, (iii) provincial-higher SES, and (iv) provincial-lower SES.*Match-pairing:* We will employ a Euclidian distance minimization strategy to create pairs of similar schools from within strata. The variables used in this minimization process will be: (i) ICSEA, (ii) school size (number of students enrolled), (iii) average scores on national standardized test of numeracy and literacy that are completed by all NSW children (see outcomes section for further details) and (iv) school participation (or not) in a state-wide physical activity and nutrition program, known as Live Life Well at School [34], that took place from 2008 to 2015.*Pair selection:* Once schools have been matched using the minimization procedure, we will select the two or three most similar pairs of schools from within each stratum to participate in the cluster RCT. Through this process, four schools will be selected from each of the provincial strata and six schools are chosen from each of the urban strata. This strategy will allow for calculation of average treatment effects and differences in treatment effects by strata.*Randomization*: Following baseline data collection, schools will be randomly assigned from within each pair to the experimental or control arm of the cluster RCT. An experienced statistician who is not part of the research team will conduct the randomization procedure using a computer-generated algorithm.

From within each cohort of 90 schools, the 80 schools not selected for the cluster RCT will be included in the scale-up implementation study.

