##### Effectiveness

We will conduct a reduced examination of effectiveness in the scale-up implementation study compared with the cluster RCT. Assessments will include all questionnaires and standaridized tests of numeracy and literacy from the cluster RCT. Other measures (e.g., 20 m multistage fitness test, accelerometers, fundamental movement skills, and cognitive control) will not be obtained in the scale-up implementation study.

Principals and teachers will complete online questionnaires. Classroom teachers will also administer an online questionnaire to their students to complete self-report measures. Questionnaires will be administered to principals, teachers, and students at baseline, post-intervention (12 months) and maintenance (24 months).

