#### Statistical analyses

The scale-up implementation study will be assessed with a focus on descriptive statistics concerning reach, adoption, implementation, and maintenance. We will also use linear regression to explore the impact of school and community characteristics on program reach. We will use linear mixed model analysis to examine changes in outcome variables from baseline to 12-months and 24-months (i.e., effectiveness). These effects will be estimated for the entire sample as well as in key sub-populations (e.g., across teacher sex, school average SES, teachers with high vs low internet self-efficacy). Where possible, we will compare *iPLAY* schools with expected values within the population (e.g., NAPLAN scores in similar schools, physical activity participation) from other data sources such as NSW School Physical Activity and Nutrition Survey [66]. We will also compare outcomes at 12 months (post-intervention) for Cohort 1 with baseline levels for Cohort 2, taking advantage of the natural experiment that is inherent in the design of the study.

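### The scale-up study sets NAPLAN against non-randomised similar schools; if a random draw of volunteer schools is oversubscribed, the undrawn volunteers are a randomised comparison group that the plan leaves unused

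*Protocol article*

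**What the plan says.** Under Recruitment, selection and randomization, all 1,600 government-funded NSW primary schools are invited. Of those that express interest before May 2016, "we will use a computer-generated algorithm to randomly select 90 to form Cohort 1". Recruitment then runs to March 2017, "at which point we will randomly select 90 schools to form Cohort 2". The recruitment goal is worded "We aim to recruit a total of 180 schools", which equals the 2 x 90 = 180 places. The expected number of interested schools is not given.

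Ten schools per cohort go to the cluster RCT, and "the 80 schools not selected for the cluster RCT will be included in the scale-up implementation study". That study has no control arm (its Economic evaluation section says so). Its Effectiveness section limits outcomes: "Assessments will include all questionnaires and standaridized tests of numeracy and literacy from the cluster RCT".

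The scale-up Statistical analyses section is mainly descriptive. Besides change from baseline, it names two external comparisons. One sets iPLAY schools, where this can be done, against "expected values within the population (e.g., NAPLAN scores in similar schools, physical activity participation" and similar survey values. The other is stated as "We will also compare outcomes at 12 months (post-intervention) for Cohort 1 with baseline levels for Cohort 2".

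Interested schools that lose the draw are not mentioned. The follow-up of outside schools under Reach covers only schools that did not volunteer, and only their reasons.

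**The concern.** A school in the scale-up study has chosen to take part. Under Participants and procedures it must also have at least half its Stage 2 teachers willing, a staff member prepared to lead, and a consenting principal. Schools that resemble it on recorded features need share none of this. A NAPLAN difference between the two groups could come from iPLAY or from being the kind of school that volunteers, and adding schools does not shrink that bias.

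NAPLAN matters here because the other scale-up pupil outcomes are questionnaires. It is also an outcome that exists for schools outside the study: the matching step describes "average scores on national standardized test of numeracy and literacy that are completed by all NSW children". A lottery among volunteers is what would hold willingness to volunteer constant. If the list of entrants is not kept when each draw is made, the comparison may be impossible to rebuild later.

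**Working it through.** **No figure to reproduce on this point.** The article's one power calculation concerns fitness in the RCT and does not bear on the scale-up NAPLAN comparison. It does reproduce: the design effect is 1 + 17 x .10 + 2 x 18 x .01 = 3.06, and 540/3.06 = 176.5 effective pupils per arm. With effect .35 and two-sided 5% (assumed), power is .908 against the stated .91.

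**Does the other planned comparison fill the gap?** By the Design section, Cohort 1 pupils are in Years 4 and 5 at 12 months, and Cohort 2 pupils are in Years 3 and 4 at baseline. Academic achievement obtains NAPLAN for Years 3 and 5 only. The tested pupils are therefore Year 5 on one side and Year 3 on the other, with no tested year in common. For NAPLAN, this comparison cannot stand in for a control group, although volunteers are on both sides.

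**Precision of a drawn-versus-undrawn comparison.** In units of the SD of school averages, SE = sqrt[(1 - r²)(1/n1 + 1/n0)]. Assumptions not in the article: r = .8 with the school's pre-draw average; both draws pooled, so n1 = 180; n0 undrawn schools; each school counted once. Then 1 - r² = .36.

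| Undrawn schools n0 | SE | Detectable at 80% power (2.80 x SE) |
|---|---|---|
| 0 | no comparison | none |
| 60 | sqrt[.36(1/180 + 1/60)] = .089 | .25 |
| 120 | .071 | .20 |
| 180 | .063 | .18 |

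With one draw only (90 drawn), the detectable difference at r = .7 is .67 for 10 undrawn, .42 for 30 and .30 for 90. At r = .9 it is .41, .26 and .18. On the same school-level scale, the 10-versus-10 RCT would detect .90 at r = .7 and .55 at r = .9, ignoring pair matching and pupil-level adjustment.

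**Dilution.** Randomisation is preserved only if all 90 drawn schools per cohort are kept, because the ten RCT schools are chosen by similarity, not at random. About 5 of each 90 become attention controls, so 85/90 = 94% of the effect remains. Drawn schools that do not take part would lower it further.

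**Crossover.** Implementation timeline starts Cohort 1 groups in June, August and November 2016 and March 2017, and Cohort 2 from June 2017, with about 10 months of delivery. The article does not say whether undrawn Cohort 1 schools re-enter the second draw. If they do and are drawn, they stop being controls when the four groups are about 12, 10, 7 and 3 months in. Year 3 pupils at baseline reach Year 5 only at 24 months. Schools never drawn remain usable throughout.

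**Illustration of the selection bias.** Suppose iPLAY has no effect, volunteers would improve by d more than similar schools anyway, and a two-sided 5% test were applied. The rejection rate is 1 - Φ(1.96 - d/SE) + Φ(-1.96 - d/SE).
- 160 iPLAY against 160 similar schools, d = .10: SE = sqrt(2/160) = .112 at r = 0 gives about 14%; SE = sqrt(.51 x 2/160) = .080 at r = .7 gives 24%.
- 160 against about 1,400 schools (1,600 - 180 = 1,420, rounded), r = .8: SE = sqrt[.36(1/160 + 1/1,400)] = .050 gives 17%, 52% and 85% for d = .05, .10 and .15.

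The spread shows how far these rates depend on the inputs. A comparison by draw stays at 5% in every case.

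**The case against.** The strongest reply is that the plan treats this as a benchmark, not a test. The scale-up analysis is described as mainly descriptive, effectiveness there is called reduced, and the population comparison is made only where feasible, with no threshold or causal claim. This stands. A reader might infer from the illustration that the plan would declare a false NAPLAN effect about half the time. The article does not support that: it states no such test, the 52% uses nearly all other schools although the article speaks of similar ones, and d and r are assumed.

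A reader might also infer that a randomised comparison is certainly there for the taking. It is not. The target of 180 equals the places, and no volunteer count is given. Random selection of 90 makes sense only with a surplus, but the article does not say that one is expected.

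Nor is all NAPLAN evidence in the project non-randomised. The cluster RCT obtains the scores and compares arms by intention to treat, although with 20 schools.

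Finally, the matching step uses school averages only for the 90 selected schools, so it does not show that the team will hold them for undrawn schools. This stands in part. The test is taken by all NSW children and the plan already intends to use scores from non-study schools, but the averages for undrawn schools would have to be requested.

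What survives is narrower. The named comparator is open to volunteer selection, no other planned scale-up analysis removes it for NAPLAN, and the article's own selection procedure may provide a better comparator.

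**Conclusion.** The point holds in conditional form. The similar-schools comparison cannot separate iPLAY from willingness to volunteer. If either draw is oversubscribed, a randomised comparison exists that the plan does not use. Its precision depends on an unstated number: SE about .06 to .09 school-level SD for 180 to 60 undrawn schools, at an assumed r = .8 with draws pooled and before crossover and dilution. With no surplus there is nothing to gain beyond more careful wording. The RCT, its primary outcome and its own NAPLAN analysis are untouched. This is a cheap improvement to one secondary strand of the scale-up study.

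**What to change.** In Recruitment, selection and randomization, state that the list of schools entered in each draw, with the result, will be kept, and whether schools not drawn for Cohort 1 re-enter the second draw.

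In the scale-up Statistical analyses section, add that if a draw is oversubscribed, school-average Year 3 and Year 5 NAPLAN will be compared between drawn and undrawn volunteers. Specify that:
- schools are analysed as drawn, with all 90 per cohort kept, including those that enter the RCT or do not take part;
- the model adjusts for the school's pre-draw average and ICSEA, with a term for the draw when both are pooled;
- schools drawn later count as controls only until Cohort 2 starts.

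Where this comparison is available, base any causal statement about NAPLAN in the scale-up study on it and on the RCT. Present similar schools as a descriptive benchmark subject to volunteer selection.

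The cost is two stored lists, school averages for the undrawn schools and one extra regression. The limits to state are that the analysis is unavailable without oversubscription, that precision is unknown until the draws are made, and that RCT controls, non-participating drawn schools and late-starting groups pull the estimate towards zero. It covers school-average NAPLAN only, since undrawn schools complete no questionnaires.

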### Cluster randomized controlled trial

We will conduct a cluster RCT with an allocation ratio of 1:1 (intervention : attention control) that conforms with CONSORT guidelines [40]. We will perform assessments at baseline, post-intervention (12 months after baseline) and maintenance (24 months after baseline).

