### Primary outcome measure – entire RCT sample

Cardiorespiratory fitness will be assessed using the 20 m multistage fitness test [42], which has demonstrated strong validity in studies worldwide [43] and is considered to be the most appropriate field-based measure [44]. We will measure cardiorespiratory fitness for all physically able children in the cluster RCT.

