##### Statistical analyses and sample size

We will test for between-arm differences in changes in student outcomes using linear mixed models with standard errors corrected for clustering. We will analyze data according to intention to treat principles (main analyses) and per-protocol principles (sensitivity analyses). We conducted a power analysis using procedures appropriate for complex nested designs [71]. In this analysis the effect size for between-arm differences in cardiorespiratory fitness (primary outcome) was conservatively set to .35 (note: effect in our efficacy trial was .54) with intraclass correlations based on our efficacy trial [21] (class = .09, school = .01). Analysis indicated that 1080 students from 60 classes in 20 schools (i.e., 3 classes per school) would provide power of .91.

We will explore potential moderators of intervention effects including children’s age, sex, ethnicity, weight status and SES, as well as baseline levels of cardio-respiratory fitness, physical activity and fundamental movement skill competence. As with the main analyses, we will employ a mixed modeling approach to explore moderation hypotheses by including appropriate interaction terms in the regression models. The trial is not powered to detect interactions; thus, we will employ a significance level of *p* < 0.1 to explore potential moderators. We will explore significant interaction terms by testing sub-groups differences on the primary outcome and selected secondary outcomes. We will also explore potential moderating effects of principal and teacher characteristics (e.g., specialist PE accreditation) on student outcomes.

Per protocol analyses will investigate the influence of *iPLAY* leaders’ and other teachers’ adoption and implementation of the intervention on student outcomes. Adoption will focus on the proportion of intervention training components completed (e.g., workshops attended and online tasks completed), while implementation will evaluate leaders’ and teachers’ utilization of strategies in their schools (as per Table 1).

Linear mixed models will be also used to examine potential mediating processes. For example, in our efficacy study we found that changes in fundamental movement skills mediated the effect of the intervention on children’s physical activity and cardiorespiratory fitness. Mediating effects will be estimated using a cluster-bootstrapped based product-of-coefficients test that is appropriate for cluster RCTs.

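### Pairing on school traits leaves baseline fitness largely to chance, so the primary model should adjust for baseline fitness rather than compare changes

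*Protocol article*

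**What the plan says.** All quotations are from the protocol article.

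- **Allocation** (Recruitment, selection and randomization for both investigations). Schools "will be stratified according to SES and geographic location". Pairing inside each stratum comes next: "The variables used in this minimization process will be: (i) ICSEA, (ii) school size (number of students enrolled), (iii) average scores on national standardized test", followed by past participation in a state-wide activity and nutrition programme. The stated aim is to balance most school-level covariates, "thereby increasing the likelihood that children in the two conditions are similar on the outcome variables at baseline". The last step reads: "Following baseline data collection, schools will be randomly assigned from within each pair to the experimental or control arm of the cluster RCT".
- **Baseline fitness** (Primary outcome measure; Cluster randomized controlled trial). "We will measure cardiorespiratory fitness for all physically able children in the cluster RCT", and "We will perform assessments at baseline, post-intervention (12 months after baseline) and maintenance (24 months after baseline"). The primary outcome has therefore been measured in each school before that school is allocated.
- **Analysis and power** (Statistical analyses and sample size). The test is of between-arm differences in changes, using linear mixed models. Power is given as .91 for 1080 pupils in 60 classes in 20 schools. The effect size "was conservatively set to .35" and the ICCs are "class = .09, school = .01".

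**The concern.** The matching is meant to make the arms more alike on the outcomes at baseline, but none of the matching variables is a fitness measure. A trait that is constant within a school can explain only the school component of variance. In this plan that component is small beside the variation between classes and pupils, so pairing can do little for the primary outcome and chance decides most of the baseline difference.

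How much this matters depends on the analysis. A comparison of changes subtracts the whole baseline difference. When baseline and follow-up correlate below 1, part of that difference would have faded through regression to the mean, so the subtraction goes too far. Precision in the primary comparison is at stake, together with how an observed baseline imbalance carries into the estimate. The validity of the randomization is not.

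**Working it through.** **Inputs.** From Statistical analyses and sample size: school ICC .01, class ICC .09, 20 schools, 3 classes per school, 1080/60 = 18 pupils per class, effect .35 SD. From the 1:1 allocation: 10 schools per arm. Assumed: two-sided 5% test, and the same ICCs at baseline as in the power calculation.

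**1. The plan's power.**
- Variance of a school mean: V = .01 + .09/3 + .90/54 = .01 + .03 + .01667 = .05667.
- SE of the arm difference = sqrt(2 × .05667/10) = .1065.
- Power = Φ(.35/.1065 − 1.96) = .908, which reproduces the stated .91. The inputs are read correctly.

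**2. What school traits can explain.**
- Share = .01/.05667 = 17.6%, or about 18%.
- School ICC .02: V = .02 + .03 + .89/54 = .06648, and .02/.06648 = 30%.
- School ICC .03 gives 39%, and .05 gives 52%.
- At school ICC .01, 2 classes per school gives 12.5% and 4 gives 22%.

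**3. Chance baseline difference between arms.**

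| Pairing explains | SD of difference | 95% range | Chance above .1 SD |
|---|---|---|---|
| None of the school component | sqrt(2 × .05667/10) = .106 | ±.21 | 35% |
| All of the school component | sqrt(2 × .04667/10) = .097 | ±.19 | 30% |

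A simulation of within-pair allocation (5 pairs in each of 2 cohorts) gave the same figures.

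**4. What a comparison of changes does with that difference.** Let r be the correlation of baseline and follow-up school means, with equal variances. A baseline difference d is expected to persist as r × d, but the change comparison subtracts d. The estimate, given d, is shifted by −(1 − r)d. For d = .1 SD the shift is .03 SD at r = .7 and .05 SD at r = .5, against a planned effect of .35. Averaged over randomizations the shift is zero. It appears as extra variance.

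**5. Gain from adjustment.** r is not given in the article; .7 to .5 is an assumed range.
- Variance under change scores is proportional to 2(1 − r). Under baseline adjustment with a known slope it is proportional to 1 − r².
- The ratio is (1 + r)/2: .85 at r = .7 and .75 at r = .5.
- Estimating the slope from 20 school means (18 residual degrees of freedom before the covariate) multiplies the adjusted variance by about 1 + 1/16 = 1.0625. The ratios become .90 and .80, a reduction of about 10% and 20%.
- Simulated SEs agree. At r = .7 the SE falls from .0833 to .0792, a variance reduction of 1 − (.0792/.0833)² = 10%. At r = .5 it falls from .1061 to .0944, a reduction of 1 − (.0944/.1061)² = 21%.
- From these SEs, power for .35 is .988 (change) and .993 (adjusted) at r = .7, and .910 and .960 at r = .5.

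**6. Gain from also constraining the allocation.** Drawing from the better-balanced 16 of the 32 within-pair allocations in each cohort cuts the SD of the baseline difference from .106 to about .048, and the chance of exceeding .1 SD from 35% to about 3%. Once baseline is adjusted for, the further reduction in variance is only about 1% to 5%. In 43% of simulated trials at least one cohort then contained two schools from different pairs that were always, or never, in the same arm.

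**The case against.** Most of the case on the other side stands.

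- **Nothing is contradicted.** The article says only that balancing school covariates makes similarity more likely. Stratified, pair-matched allocation by an independent statistician is sound, and what remains is chance that the standard error covers. A reader might infer that the allocation is biased or that the plan breaks a promise of balance. The text supports neither.
- **The trial is not short of power on its own terms.** The .91 takes no credit for baseline data, and the change analysis still gives .91 at r = .5. The loss is of available precision.
- **The 18% is not a firm ceiling.** It rests on one school ICC from the efficacy trial. Spreading schools across SES and location strata could raise it, as step 2 shows.
- **Constrained randomization is not the main remedy.** A reader might see baseline data left unused before allocation and conclude that the allocation must change. After adjustment the gain is small, and a tight constraint on five pairs can lock pairs together.
- **The handling of baseline may be settled in an analysis plan that is not shown.** This is fair. A longitudinal mixed model with a common baseline mean in both arms already behaves like baseline adjustment. The point applies if the stated test means an unadjusted comparison of changes, or a model in which each arm has its own baseline mean. The wording admits that reading and should exclude it.

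**Conclusion.** The point holds as an inexpensive improvement of low severity. On the plan's own ICCs, pairing on school traits can address only about 18% of the variance of a school's mean fitness (30% at a school ICC of .02). Baseline differences between arms of about .1 SD are therefore ordinary: SD .10 to .11, with a 30% to 35% chance of exceeding .1 SD. They are chance, not bias. A plain comparison of changes handles them inefficiently, and adjusting for baseline lowers the variance of the effect estimate by about 10% to 21%.

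This rests on the efficacy-trial ICCs applying at baseline, on 3 classes of 18 per school, on an assumed school-mean correlation of .7 to .5, and on reading the stated test as an unadjusted comparison of changes. The gain shrinks as r approaches 1. Below r = .5 a change score is less precise than ignoring baseline altogether, since 2(1 − r) then exceeds 1.

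**What to change.** **Main change, in Statistical analyses and sample size.** Replace the test of differences in changes for the primary outcome with wording such as: 'The primary analysis is a linear mixed model for 12-month cardiorespiratory fitness, with fixed effects for arm and the pupil's baseline fitness and random effects for school and class.' School-mean baseline fitness may be added as a second covariate. The 10% to 21% was worked out for adjustment on school means; the gain from the pupil value alone was not calculated. The cost is a sentence of text and one or two model parameters. No schools, pupils or measurements are added.

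**Optional, in the randomization step.** The independent statistician may compute each school's mean baseline fitness and, within each cohort, exclude only the worst-balanced within-pair allocations before drawing one at random. The statistician should check that no two pairs are locked together. This mainly improves face validity and adds a few percent of precision at most beyond adjustment. Its cost is that baseline fitness must be entered before each cohort is allocated.
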